## Abstract

**Background:**

Cerebral palsy is the most common physical disability of childhood and early detection is possible using evidence based assessments. Systematic reviews indicate early intervention trials rarely demonstrate efficacy for improving motor outcomes but environmental enrichment interventions appear promising. This study is built on a previous pilot study and has been designed to assess the effectiveness of a goal - oriented motor training and enrichment intervention programme, “GAME”, on the motor outcomes of infants at very high risk of cerebral palsy (CP) compared with standard community based care.

**Methods/design:**

A two group, single blind randomised controlled trial (n = 30) will be conducted. Eligible infants are those diagnosed with CP or designated “at high risk of CP” on the basis of the General Movements Assessment and/or abnormal neuroimaging. A physiotherapist and occupational therapist will deliver home-based GAME intervention at least fortnightly until the infant’s first birthday. The intervention aims to optimize motor function and engage parents in developmental activities aimed at enriching the home learning environment. Primary endpoint measures will be taken 16 weeks after intervention commences with the secondary endpoint at 12 months and 24 months corrected age. The primary outcome measure will be the Peabody Developmental Motor Scale second edition. Secondary outcomes measures include the Gross Motor Function Measure, Bayley Scales of Infant and Toddler Development, Affordances in the Home Environment for Motor Development – Infant Scale, and the Canadian Occupational Performance Measure. Parent well-being will be monitored using the Depression Anxiety and Stress Scale.

**Discussion:**

This paper presents the background, design and intervention protocol of a randomised trial of a goal driven, motor learning approach with customised environmental interventions and parental education for young infants at high risk of cerebral palsy.

**Trial registration:**

This trial is registered on the Australian New Zealand Clinical Trial register: ACTRN12611000572965.

## Background

Cerebral palsy (CP) is the most common physical disability of childhood with a prevalence of 2.1/1000 live births [1]. Late diagnosis, conservative “wait and see” monitoring and late referral to early intervention is the prevailing norm for two main reasons. First, because only half of infants with CP have clearly identifiable risks in the newborn period, for example prematurity or neonatal encephalopathy (NE) [2], and second, because not all infants with prematurity or NE will go on to have CP. Wait and see monitoring can mean brain injured infants do not always receive intervention in the most crucial period of brain development [2]. Furthermore children with CP reach approximately 90% of their gross motor potential by age 5 (or younger for more severely impaired), but for 40% of this critical window the ultimate severity of their condition is largely unknown [3], however severity itself is a likely predictor of responsivity to early intervention. The field of neuroscience has repeatedly demonstrated the plasticity of the infant brain and persistence of neurogenesis and activity- dependent plasticity are two of the basic mechanisms at work [4]. Intervention for infants with brain injuries aims to optimise these neuroplastic mechanisms.

In recent years, research into the predictive validity of Prechtl’s Qualitative Assessment of General Movements (GMs) has allowed earlier diagnosis of high risk of CP to be reliably made at 3 months of age [5,6]. GMs is now the gold standard tool for early diagnosis of CP because of higher specificity and sensitivity than other traditional tests such as neurological examinations, cranial ultrasound and MRI [7]. For the preterm population, the combination of GMs and evidence of white matter injury on MRI predicts CP at 3 months with 100% accuracy [6].

### Early intervention and early enrichment

Early intervention (EI) studies have typically not used this combination of assessment tools to recruit homogenous samples of infants at high risk of CP. Rather heterogeneous infants are included in EI studies and labelled “high risk” because they were preterm, display delayed development or had complex social issues [8]. In many of these studies the proportion of children who actually go on to be diagnosed with CP are relatively small resulting in underpowered type II trials for CP. As a result it is virtually impossible to ascertain the effects of EI on the motor outcomes of infants with CP. Most systematic reviews conclude that EI approaches currently in use for CP do not have any effect on motor outcomes greater than what would be expected as a result of maturation [9,10]. It is important to note, however, that evidence for the effectiveness of general EI to improve cognition is well established for the more heterogeneous “high risk” groups [11].

It remains to be determined whether intervention approaches that are goal-oriented and involve active motor training [12,13] currently used in older children with CP are actually applicable to infants with a small emergent motor repertoire. In addition, what “active ingredients” from EI approaches are vital to maximise developmental outcomes?

Environmental enrichment (EE) has been proven to enhance neuroplasticity and promote memory and motor function in animal studies [14] but the effect in humans is less understood. In animal studies, an EE is defined as one that facilitates enhanced cognitive, motor and sensory stimulation. Although there is no agreed parameters for enrichment, these animal housing conditions typically include high levels of complexity and variability with arrangement of toys, platforms and tunnels being changed every few days to promote motor learning and memory. The motor opportunities afforded by EE are a critical success factor.

Translating these ideas into the human context is complex. Much more is known about the detrimental impact of deprivation (under-enrichment) on child development than is known about what constitutes enrichment for infants raised in “expected environments” [15]. Thus a continuum of enrichment is implied, but has not been well explained in terms of the type or amount of enrichment required for children who are not typically developing. One recent systematic review [8] has demonstrated a small positive effect on motor outcomes for infants at high risk of CP when the utilised interventions are based on principles of environmental enrichment. The enhanced plasticity mechanisms present in the infant brain allow it to be more strongly influenced by the environment than adult brains, so furthering our understanding of what constitutes enrichment for brain injured babies is important [16,17].

In children with CP the key environmental factors which influence motor development are yet to be determined, however clinical and neuroscience do provide a clear rationale for the urgent need for the development of EI programmes that focus on EE strategies to improve motor outcomes in these children [18]. Ulrich’s [19] recent review discusses the opportunities for the development of early intervention programs which link neuroscience with clinical science and states in her summary, “A growing body of basic and clinical science results suggest we are missing the boat on opportunities for infants with motor disabilities if we do not develop more empirically based protocols to use very early in life in order to optimize developmental outcomes” [19], p10.

We have developed such a protocol, “GAME”, based upon the principles of motor learning and widely accepted EI frameworks including family centred practice [20] and the ecological framework [21]. Data from our recent pilot randomised controlled trial RCT (n = 13) indicates that GAME, a goal-oriented, intensive motor training programme that actively involves parents and includes EE strategies, could be effective in advancing the motor trajectories of infants at high risk of CP [22]. After 12 weeks, GAME intervention infants (n = 6) had an 8.05 point advantage on the Total Motor Quotient of the Peabody Developmental Motor Scales – second edition compared to infants who received standard care therapy (n = 7). Although small, the pilot study confirmed feasibility of recruitment and randomisation procedures, and enabled confirmation of outcome measures and the sample size required for a larger RCT of GAME intervention. This proposed study will address this gap in the literature.

### Objective

The aim of this study is to evaluate whether a goal oriented, intensive motor training programme with EE strategies (GAME) is more effective than current standard care practices in influencing the early motor development of infants at high risk of CP.

## Methods

A single blind RCT with 2 parallel groups will be conducted to evaluate the efficacy of GAME compared to standard care. The outcomes of this trial are the infant’s motor function after 16 weeks of intervention and at 12 and 24 months corrected age, home enrichment, parent perception of and satisfaction with their child’s performance and parental well - being.

We hypothesise that:Infants diagnosed with CP or at risk of CP that receive GAME intervention will have higher short term (after 16 weeks of intervention) Peabody Developmental Motor Scale (PDMS II) scores than infants that receive standard careInfants diagnosed with CP or at risk of CP that receive GAME intervention will have higher long term (at 1 year of age) scores on the PDMS II scores than infants that receive standard care.Infants diagnosed with CP or at risk of CP that receive GAME intervention will have higher Gross Motor Function Measure (GMFM) scores than infants that receive standard care at 1 year of age.Infants who have received GAME intervention will have sustained higher PDMS –II scores long term (at 24 months) compared with infants who have received standard care.

### Study sample and recruitment

Thirty infants will be recruited from their treating institution, community physician or local therapist. The infants will be recruited in and around Sydney, NSW Australia. Seven NICUs and the Cerebral Palsy Alliance will actively recruiting to this study although infants may be referred from any source. Study sites are listed in the Appendix.

All parents of eligible infants will be informed about the study only after they have had discussions with their medical team regarding the high risk status of their child, or a confirmed diagnosis of CP. Families will be given a site specific information sheet regarding the purpose and design of the study and have opportunity to speak with investigators before consenting to the study. Parents who do not wish to consent to the study will be offered standard community based therapy.

After consent is obtained, prior to randomisation, the investigators will visit the family at home to complete all baseline assessments and collect demographic and perinatal data. MRI and medical data will be obtained from the infant’s medical record.

The Human Research and Ethics Committees of the Sydney Children’s Hospital Network (SCHN), Cerebral Palsy Alliance (CPA) and the University of Notre Dame Australia (UNDA) have approved this study. The experimental design including time points and outcome measures are depicted in the CONSORT [23] flowchart (Figure 1).

**Figure 1 Fig1:**
[figure not shown]
**Consort flow chart.**

### Inclusion criteria

Infants aged between 3 and 6 months (corrected age) with a diagnosis of CP or at high risk of CP are eligible for the study. Infants referred between 9–18 weeks post term age (PTA) will be screened using the General Movements Assessment (GMs). At least 2 certified assessors blinded to the infant’s history will score the GMs videos. Infants with abnormal general movements (absent fidgety) are eligible for enrolment, ie 95% high risk of CP. Where assessors disagree, a third blinded assessor will be required to assess the video.

Infants over 18 weeks corrected age up to 6 months of age, outside the window of reliable GMs assessment, will be included on the basis of a confirmed CP diagnosis and/or abnormal neuroimaging as described by Krageloh-Mann [24].

Imaging commonly associated with CP include:Periventricular Leucomalacia (PVL) and cystic PVLIntracranial HaemorrhagePeriventricular infarctionLesions of the basal ganglia and thalamusUnilateral parenchymal injury eg middle cerebral artery infarctionCortical malformation

A pediatric neurologist blinded to group allocation will confirm MRI features.

### Exclusion criteria

Infants otherwise eligible but with severe genetic abnormalities, or not discharged from hospital, or residing in remote areas not accessible to the research team will not be eligible for the study.

### Sample size

The planned study sample size (n = 30; 15 per group) has been estimated from a power calculation based on our pilot data using motor composite scores of the PDMS-2, with an alpha value of 5% and power of 80%, using a minimal clinically important difference of 10%, accounting for a 20% dropout rate.

### Randomization process

After informed consent and baseline measures are taken, an officer not connected with the study will randomise participants at a separate location using a pre-prepared random assignment schedule stored within 30 concealed opaque envelopes generated using computer generated random numbers. The Primary Investigator will be informed by the independent randomisation officer of group allocation and will inform parents. Twins will be randomised together due to the nature of the intervention.

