### Statistical methods

Analysis will be conducted on an intention-to-treat basis using SPSS and reported according to the CONSORT statement. Descriptive statistics (frequencies, means and 95% CIs) will be used to describe the sample at baseline and data from each outcome measure used will be summarised for both treatment groups. Between-group differences following intervention will be analysed using multiple regression to determine whether group allocation predicts outcome. MRI classification, SES and comorbidities including vision impairment and epilepsy will be considered as covariates in the analysis.

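### Twin pairs are allocated as one unit, but neither the named regression nor the sample size provides for within-pair correlation

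*Protocol article*

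**What the plan says.** Three places in the protocol article bear on this.

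- **Randomization process:** "Twins will be randomised together due to the nature of the intervention". Singletons are allocated individually, and a pair goes to one arm as a unit.
- **Statistical methods:** "Between-group differences following intervention will be analysed using multiple regression to determine whether group allocation predicts outcome". The covariate list follows: "MRI classification, SES and comorbidities including vision impairment and epilepsy will be considered as covariates in the analysis". Family or twin membership is not in it, and no method for correlated observations is named.
- **Sample size:** "The planned study sample size (n = 30; 15 per group) has been estimated from a power calculation". Alpha is 5%, power 80%, the target difference 10%, and dropout is handled by "accounting for a 20% dropout rate". The unit counted is the infant, and no allowance for pairs is mentioned.

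The article does not say how many twin pairs are expected or how strongly outcomes are thought to correlate within a pair.

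**The concern.** An analysis should respect the unit that was randomised. Twins allocated together share the arm, the home where GAME visits take place, and the parents who carry out most of the practice, so their motor scores are likely to be positively correlated. Regression without a family term or adjusted variance treats their residuals as independent. It credits a pair with two infants' worth of information when it carries less. The standard error of the group effect then comes out too small, the nominal 5% test rejects too often under the null, and the true information falls short of what the infant count suggests.

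Twins are foreseeable here, since the authors wrote a rule for them and seven NICUs are among the recruiting sites. For two secondary measures the dependence is almost built in. The DASS-21 describes the parent and the AHEMD-IS describes the home, so a per-infant analysis could enter one parent or one home twice.

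**Working it through.** **Inputs from the article.** 30 infants, 15 per group; alpha 5% (taken as two-sided, as no sidedness is given); power 80%; dropout 20%, so 30 × 0.8 = 24 evaluable.

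**Assumptions, not in the article.** Number of complete evaluable pairs k = 0, 1, 3 or 5; ICC within a pair = 0.3 to 0.8.

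**Step 1: the plan's own figure.** The sample size of 30 can be neither confirmed nor refuted, because no standard deviation is given. Read the 10% difference as 10 points (an assumption). Then n per arm = 2 × (1.960 + 0.842)² × SD² / 10², divided by 0.8 for dropout. This gives 15 per arm only if the SD is about 8.4 to 8.7. With SD 8.5, for example, n = 11.3, rounded up to 12, and 12 / 0.8 = 15. Nothing in this needs or contains a term for pairs.

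**Step 2: design effect.** With k pairs among N infants in two equal arms, each pair adds a covariance term to the variance of its arm mean. The variance of the difference between arms is multiplied by

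DEFF = 1 + ICC × (2k/N),

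however the pairs fall between the arms.

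**Step 3: consequences at N = 24.**
- Type I error of a nominal 5% test that ignores pairing: 2 × [1 − Φ(1.960/√DEFF)].
- Power of a test that keeps its 5% level, when the design had exactly 80% for independent infants: Φ((1.960 + 0.842)/√DEFF − 1.960).

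| Pairs | ICC | DEFF | True SE / model SE | Type I error | Power |
|---|---|---|---|---|---|
| 0 | any | 1.000 | 1.00 | 5.0% | 80.0% |
| 1 | 0.3 | 1.025 | 1.01 | 5.3% | 79.0% |
| 1 | 0.8 | 1.067 | 1.03 | 5.8% | 77.4% |
| 3 | 0.3 | 1.075 | 1.04 | 5.9% | 77.1% |
| 3 | 0.8 | 1.200 | 1.10 | 7.4% | 72.5% |
| 5 | 0.3 | 1.125 | 1.06 | 6.5% | 75.2% |
| 5 | 0.8 | 1.333 | 1.15 | 9.0% | 68.0% |

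Worked line: k = 3, ICC = 0.8 gives DEFF = 1 + 0.8 × 6/24 = 1.20 and √1.20 = 1.095. Then 1.960/1.095 = 1.789, which has a two-sided tail of 7.4%.

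**Step 4: simulation check.** Families were randomised and arms compared with an unadjusted t-test, 40,000 replicates per setting at N = 24. Type I error was 5.5% and 5.8% with one pair (ICC 0.3 and 0.8), 5.8% and 7.2% with three, and 6.5% and 8.6% with five. This is within about 0.3 percentage points of the formula.

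**Step 5: with all 30 infants retained.** The effect is a little smaller: 5.2% to 5.6% with one pair, 5.7% to 6.9% with three and 6.2% to 8.2% with five.

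**The case against.** The strongest reply is that this is a condensed article with one sentence on the model. Robust errors or a family term could sit in a full analysis plan that is not shown. That stands as a limit on what can be claimed. A reader might infer that the article commits to ordinary regression with twins as independent infants, or that it reports standard errors that are too narrow. It does neither: it uses no such words and states no standard error for the treatment effect. What remains is that the article fixes both the allocation rule and the model with its candidate covariates, and the second does not follow from the first.

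The harm is also conditional. A reader might infer that the type I error will exceed 5% and that 80% power is lost. This happens only if both twins of a pair qualify, enrol and are evaluable. Each must meet the inclusion criteria and be discharged from hospital. With one or two pairs the effect is small, and the 9.0% figure needs 10 of 24 infants to be twins with an ICC of 0.8. The calculations use no covariates. SES is shared by twins and MRI class may be, so adjustment could lower the residual correlation.

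Two further readings are not supported. Recruitment is not stated to be mainly from NICUs: the article also names the Cerebral Palsy Alliance, community physicians and local therapists, and accepts referral from any source. Nor are the 30 envelopes an error. The article does not say that each infant uses one, and a pair drawing one envelope merely leaves one over. At most the arms may depart slightly from 15 each.

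**Conclusion.** The point holds in a limited form. Pair allocation is not carried through to the analysis named or to the sample size stated. Followed as written with complete pairs enrolled, the test is modestly anti-conservative. Across one to five pairs and an ICC of 0.3 to 0.8 at 24 evaluable infants, the type I error runs from about 5.3% to 9.0%, and nominal 80% power falls to between about 79% and 68%. The direction needs only a positive within-pair correlation; the size rests on assumed pair counts and ICCs. This should be fixed, but it does not by itself invalidate the design.

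**What to change.** - **Statistical methods:** keep the planned regression and its covariates, and account for family as the randomised unit. Use either a random family intercept with Kenward-Roger or Satterthwaite degrees of freedom, or cluster-robust errors with a small-sample correction.
- **Sensitivity analysis:** repeat the comparison with one twin per pair. This matters because the family variance is poorly estimated with few pairs. In a check by simulation with one or three pairs among 24 infants and an ICC of 0.3 or 0.5, restricted maximum likelihood put it at zero in about 17% to 31% of datasets.
- **Sample size:** state the expected number of pairs k and the assumed ICC, and give power with the design effect 1 + ICC × (2k/N).

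The cost is wording, slightly wider confidence intervals and slightly lower stated power. If no pair enrols, the planned regression is in effect unchanged.

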#### Blinding arrangements

The independent assessors will be blinded to group allocation and will carry out all assessments after randomisation. Assessments of the child’s movement for the primary outcome measure and GMFM-66, will be completed via scoring from video. Other secondary outcome measure assessments will be conducted over the phone, via home visit or parent self report, as per the test and clinical conventions. Research Assistants from the Cerebral Palsy Alliance Research Institute and trained physiotherapists and/or occupational therapists will score the measures as the blind assessors.

It is not possible for either the participating families or those conducting the intervention to be blinded in this trial due to the nature of the intervention.

### Interventions

**GAME** is a therapy intervention based on contemporary motor theory. This intervention approach has been previously described in a small pilot RCT that tested the feasibility of GAME [22]. GAME intervention consists of three components: goal-oriented intensive motor training, parent education, and strategies to enrich the child’s motor learning environment. Although described as distinct aspects of GAME, these components are fully integrated into therapy sessions with the emphasis on any particular component varying from session to session.

#### Game part 1

##### Goal-oriented intensive motor training

Families collaborate with the therapists to determine a set of goals for their child’s development [25]. Typically the goals would relate to motor development but might also include health related concerns known to affect development such as sleeping and feeding. The therapist plays an important role in helping parents set realistic and appropriately time framed goals. As goals are attained the family and therapist work together to develop new goals. These parent identified goal areas are targeted for practice during therapy sessions and built into a home programme (HP).

The motor learning component of the intervention is based on the principles of motor learning and dynamic systems theory [26,27]. Therapist assessment of the relative contributions of weakness, selective motor control and altered tone to difficulties in goal achievement are discussed with the family and solutions are identified and tried [28]. Parents are encouraged to use their knowledge of their child’s play preferences to elicit self-generated motor activity. Minimal manual guidance is provided when required and withdrawn as soon as the child has the idea of the movement or begins to demonstrate the ability to recruit a successful muscle action or sequence. Parents are coached in understanding “missing components” of the desired action and problem solve with the therapists ways of simplifying the task to enable at least part task attainment.

Motor tasks are scaffolded, so that the infant can always actively complete at least a part of the task [29]. As performance improves, the motor challenge is increased by altering the task or environment to encourage problem solving. Manual assistance is reduced or withdrawn as soon as the infant demonstrates self-initiated progress with the task; ensuring self-generated motor activity is promoted in all practice sessions. Once a motor skill is learned, variability of practice is introduced to increase the complexity and generalizability of the skill [30]. Early weightbearing and sit to stand from the parents’ lap are routinely included for each infant even if standing is not identified as a specific goal. Rehabilitation research in older children and adults with brain injuries suggest that functional weight bearing exercises can both improve motor control and provide strength training [26]. Given that the expected impairments of CP include weakness and reduced selective motor control, early activation of muscles of the lower limb using both concentric and eccentric exercise could enhance the development of upright mobility. Similarly, practice of reaching and grasping a variety of objects is also a standard part of motor training for all infants in order to expose the infants who are expected to be delayed, to a variety of objects to advance grasp and reach behaviours [31]. Modified constraint induced movement therapy and/or bimanual training is used when asymmetrical hand function is evident.

Practice schedules are discussed and designed based on family time constraints. A written HP, illustrated with photographs and related to parent identified goals, weightbearing and reach and grasp is provided. The HP describes parenting strategies, environmental enrichments and child-activities as per published guidelines on effective home programmes [32]. Activities in the HP are organised into those in which the carer plays an active role and those where practice can be “set up” for the infant to carry-out independently. The HP is updated as goals are attained.

#### Game part 2

